**Figure 1 F1:**
[figure not shown]
COPD disease trajectory.

This uncertain prognosis makes it difficult for clinicians to initiate discussions about palliative care and end–of–life care planning [19,20]. In stable COPD, population models of 6 month survival do exist but they are of limited value to predict death for individual patients [21]. It is therefore proposed to address proactive palliative care at certain milestones in the course of the disease [22], such as the occurrence of an acute exacerbation COPD (AECOPD) [20]. An AECOPD is defined as ‘an acute worsening of the patient’s condition from the stable state, which is sustained and may warrant the patient to seek additional treatment’ [23]. Exacerbations cluster in time with a high risk of recurrence within 8 weeks of recovery [24], and show an increasing frequency as the disease progresses [25]. Recovery after an AECOPD is often to a suboptimal condition as before the exacerbation and after each exacerbation more care may be required to support the patient and the family. Therefore each admission to the hospital for an AECOPD creates an opportunity to identify patients at high risk of subsequent readmission or post-discharge mortality and hence who can benefit from a proactive palliative care approach. Several studies focused on the identification of predictive factors associated with hospital readmission or mortality for patients with an AECOPD. The findings of these studies are summarized in a recent review [26]. One of the conclusions is that in-hospital mortality is related to the patient’s acute physiological state and to the development of acute comorbidity while post-discharge mortality particularly reflects the severity of the underlying COPD, as well as concomitant specific comorbidities. Important factors influencing the frequency of readmission include functional limitation and poor health-related quality of life. A profile emerges of the types of patients hospitalized for an AECOPD at high risk of subsequent readmission or post-discharge mortality [19].

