### Study parameters

#### Outcome measures indicator study

1. Primary outcome measures:

a. Length of time from the moment that a patient hospitalized for AECOPD meets two or more criteria of the set of indicators to death for any cause.

2. Secondary outcome measures:

a. Length of time from the moment that a patient hospitalized for AECOPD meets two or more criteria of the set of indicators to the first unexpected readmission to the hospital for AECOPD.

b. The sensitivity and specificity of the set of indicators, that indicate the start of proactive palliative care for patients hospitalized for COPD, in predicting death for any cause within 1 year.

c. The sensitivity and specificity of the set of indicators, that indicate the start of proactive palliative care for patients with COPD, in predicting the first unexpected readmission to hospital for AECOPD within 8 weeks.

d. Length of time from the moment that a patient hospitalized for AECOPD meets two or more criteria of the set of indicators to death as a result of pulmonary insufficiency.

e. The sensitivity and specificity of the set of indicators, that indicate the start of proactive palliative care for patients hospitalized for COPD, in predicting death as a result of pulmonary insufficiency within 1 year.

f. The contribution of individual indicators (or clusters), in predicting death for any cause within 1 year.

g. The contribution of individual indicators (or clusters), in predicting the first unexpected readmission to hospital for AECOPD within 8 weeks.

h. The contribution of individual indicators (or clusters), in predicting death as a result of pulmonary insufficiency within 1 year.

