#### Controlled trial (assessment)

##### Patient

Patients in the control condition will receive standard care (usual care) only. Patients in the intervention condition will receive standard care and, only if they meet two or more criteria of the set of indicators for proactive palliative care they will receive proactive palliative care integrated with standard care. The procedure in the control condition will be first described before describing the procedure in the intervention condition.

In the hospitals in the control condition eligible patients will be recruited the second day after hospital admission. The treating lung specialist will give each eligible patient oral and written information about the study. The written information consists of an information leaflet and two informed consent forms: one for the patient and one for the informal caregiver. In the information leaflet a description of the study, including the nature of participation and phone numbers for study contacts, are given for the patient and the informal caregiver. The lung specialist will obtain written informed consent from the patient prior to enrollment. If a patient has consented, a lung nurse will distribute questionnaires for completion on the sixth day of hospital stay or in case the patient is discharged earlier on the day before leaving the clinic. After hospital discharge the patient will be asked by the study coordinator to complete questionnaires every 3 month until the end of the study or until death. The questionnaires will be sent to the patient by mail. A stamped retour envelope will be enclosed.

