In the hospitals in the intervention condition the same procedure will be followed as in the hospitals in the control condition. In addition lung specialists will check if a patient meets two or more criteria of the set of indicators for proactive palliative care on the sixth day of hospital admission or in case the patient is discharged earlier on the day before leaving the clinic. If so, the lung specialist will inform the specialized palliative care team. Patients who are assigned for proactive palliative care will preferably meet for the first time with a physician of the specialized palliative care team before being dismissed from the hospital. If this is not possible the first meeting will take place within 1 week after enrolment. Thereafter, the specialized palliative care team will meet with the patient monthly in the outpatients setting for at least 1 year or until death.

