##### Lung specialist

The treating lung specialist will provide standard care (usual care) to the patients hospitalized for an AECOPD. After the patient has filled out and returned the questionnaires the lung specialist in the control- and the intervention condition will fill out a case report form (CRF). The CRF consists of questions about the measurement results of each indicator of the set of indicators. The set of indicators is represented in Table 1. Only in the intervention condition the lung specialist will check if a patient meets two or more criteria of the set of indicators for proactive palliative care.

**Table 1 T1:** Set of indicators for proactive palliative care

**A patient hospitalized for AECOPD is eligible for proactive palliative care when meeting two or more criteria of the following set of indicators:**	
1.	Hypoxaemia or hypercapnia at discharge
2.	Treatment of the exacerbation with Non Invasive Ventilation (NIV)
3.	Patient needs professional home care service for personal care after discharge
4.	Negative answer to the surprise question: ‘Would I (as lung specialist) be surprised if this patient would have a subsequent readmission for AECOPD within 8 weeks and/or would die in the next year?
5.	The diagnosis of a severe comorbidity such as:
	a. Non-curable malignity or
	b. Cor pulmonale (proven or non proven) or
	c. Proven Chronic Heart Failure (CHF) or
	d. Diabetes mellitus with neuropathy or
	e. Renal failure, clearance < 40 (GFR: in ml/min)
6.	CCQ total, day version ≥ 3
7.	MRC dyspnea = 5
8.	FEV1 (measured before AECOPD) < 30% of predicted
9.	BMI < 21 or unplanned weight loss (> 10% weight loss in last 6 months or > 5% in last month)
10.	Previous hospital admissions for AECOPD (last 2 years ≥ 2 and/or last year ≥ 1)
11.	Age > 70 years

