**Medical files**						
Number of hospitalisations of unexpected hospital admissions for AECOPD						X
Number of days of unexpected hospital admissions for AECOPD						X
Number of hospitalisations of unexpected ICU admissions for AECOPD						X
Number of days of unexpected ICU admissions for AECOPD						X
Are the choices of ACP documented in the medical file at baseline? (when yes/when no)						X
Are the choices of ACP documented in the medical file after one year or at time of death? (when yes/when no)						X
Did the patient die within one year after inclusion? (when yes/when no)						X
Date of death						X
Place of death (ICU/hospital/hospice/nursing home/at home)						X
Is preferred place of death known? (when yes/when no)						X
Has this wish come true? (when yes/when no)						X
Primary cause of death (pulmonary insufficiency/other cause)						X
Secondary cause of death (pulmonary insufficiency/other cause)						X
Did the patient have an unexpected hospital readmission for AECOPD within 8 weeks? (when yes/when no)						X
Date of first unexpected hospital readmission for AECOPD.						X

B = baseline; m = month; R = retrospectively.

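### Indicator-study outcomes lack a common time origin: time to readmission starts before discharge and has no start for patients with fewer than two indicators, while one-year death is dated from inclusion

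*Protocol article*

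**What the plan says.** All references are to the protocol article.

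- **Time to unexpected AECOPD readmission** (Outcome measures indicator study, item 2a among the secondary outcomes): "Length of time from the moment that a patient hospitalized for AECOPD meets two or more criteria of the set of indicators to the first" such event. The primary time-to-death outcome (1a) and time to death from pulmonary insufficiency (2d) use the same starting moment.
- **When the criteria are checked** (Controlled trial, Patient): "on the sixth day of hospital admission or in case the patient is discharged earlier on the day before leaving the clinic". This describes the intervention hospitals. The section on the lung specialist adds: "Only in the intervention condition the lung specialist will check if a patient meets two or more criteria". Control hospitals record the indicator results on the case report form but make no formal check.
- **8-week readmission**: secondary outcome c is accuracy "in predicting the first unexpected readmission to hospital for AECOPD within 8 weeks", and the Table 2 item reads "Did the patient have an unexpected hospital readmission for AECOPD within 8 weeks". Neither says from when the 8 weeks run.
- **One-year death**: Table 2 asks "Did the patient die within one year after inclusion". Inclusion happens during the stay, because "eligible patients will be recruited the second day after hospital admission".
- **Purpose of the set**: the abstract says it identifies patients at risk of dying after discharge. The Background section on identification separates the two kinds of death: in-hospital mortality follows the acute state, whereas "post-discharge mortality particularly reflects the severity of the underlying COPD".

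**The concern.** The first objective of the indicator study is the discriminating power of the set, so its results depend on when each clock starts and which events count. Three features of the stated definitions work against that objective.

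First, time to readmission begins while the patient is still in hospital and not at risk. Every patient has some event-free time built in, and more of it with a longer stay.

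Second, an origin at meeting two criteria does not exist for a patient who never meets two. As defined, the time-to-event outcomes cannot set indicator-positive against indicator-negative patients, and that comparison is what discrimination means.

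Third, deaths in the index stay can enter the one-year mortality result. By the article's own account these deaths have different determinants from the post-discharge deaths that the set was built to find.

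**Working it through.** The article gives no sample size, event rate or accuracy target for the indicator study, so there is no planned figure to reproduce. The check compares the definitions and then illustrates the size on assumed rates.

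**1. The origins side by side**

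| Outcome | Stated origin | Exists for patients with fewer than two indicators? |
|---|---|---|
| Time to death, any cause (1a) | Meeting two or more criteria | No |
| Time to first AECOPD readmission (2a) | Meeting two or more criteria | No |
| Time to death, pulmonary insufficiency (2d) | Meeting two or more criteria | No |
| Readmission within 8 weeks (2c, Table 2) | None stated | Not determinable |
| Death within one year (Table 2) | Inclusion | Yes |

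**2. Is the patient at risk of readmission at the origin?** The check is made on day six or on the day before an earlier discharge, so it always precedes discharge. Taken literally, the moment of meeting two criteria can come earlier still: age over 70 and previous admissions (Table 1, items 11 and 10) can both be true on arrival. Item 1, by contrast, is assessed at discharge and may not yet be known on day six. Items 1 and 3 cannot be observed as written for a patient who dies in the index stay.

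**3. If the 8-week item used the same origin.** This is one possible reading; the article does not state it. The share of the window spent in hospital is (days between check and discharge) / 56:
- 1 day: 1/56 = 1.8%
- 5 days: 5/56 = 8.9%
- 8 days: 8/56 = 14.3%
- 14 days: 14/56 = 25%

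One day applies to patients discharged before day six. The longer values are assumptions, since no length of stay is given.

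**4. Effect on accuracy for 8-week readmission.** All inputs are assumed: 40% indicator-positive; 8-week readmission risk of 30% in positives and 15% in negatives; 8-week death risk of 5% to 20% in positives and 1% to 3% in negatives; 1 to 10 hospital days after the check. With constant hazards h_r = −ln(1 − readmission risk)/56 and h_d = −ln(1 − death risk)/56, the observed readmission risk over T days is h_r/(h_r + h_d) × [1 − exp(−(h_r + h_d)T)].

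- Clock at discharge, no competing death: sensitivity 0.4×0.30 / (0.4×0.30 + 0.6×0.15) = 0.12/0.21 = 57.1%; specificity 0.6×0.85 / (0.6×0.85 + 0.4×0.70) = 0.51/0.79 = 64.6%.
- Clock at discharge, deaths scored as no readmission: sensitivity 55.0% to 56.7%, specificity 63.7% to 64.3%.
- Deaths scored that way and the clock started in hospital (T = 56 minus the hospital days): sensitivity 55.0% to 57.1%, specificity 63.2% to 64.3%. Observed readmission in positives falls from 30% to between 23% and 29%.

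The largest shifts are 57.1 − 55.0 = 2.1 points of sensitivity and 64.6 − 63.2 = 1.4 points of specificity.

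**5. One-year death.** Moving the origin by 4 to 12 days changes little: 4/365 = 1.1% to 12/365 = 3.3% of the window. Which deaths count could matter more. Suppose 1% to 5% of included patients die in the index stay and 15% to 25% die after discharge within the year (both assumed). The in-hospital share is then between 0.01/(0.01 + 0.25) = 3.8% and 0.05/(0.05 + 0.15) = 25%.

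**The case against.** The strongest defence is that an in-hospital origin is sensible for death. The indicators trigger a decision made during the stay, and a first palliative contact before discharge is preferred. Starting the clock when a prediction rule is applied is ordinary practice, whereas restricting to patients discharged alive conditions on something unknown at the decision. The hypothesis in the Background concerns patients hospitalized for an AECOPD and is not limited to events after discharge. This argument stands: moving the death origin to discharge would change the estimand, and the documents do not require it. It does not excuse two different origins for death, nor an origin that indicator-negative patients lack. It also does not help readmission, which cannot happen before discharge.

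A reader might go further in three ways that the documents do not support.

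- **Early deaths are scored as not readmitted.** Nothing says so. It would be inferred from a yes/no item and a logistic regression. Table 2 also collects the dates of death and of first readmission, so such deaths can be handled, and the rule may sit in the full protocol or analysis plan.
- **Long-stay patients lose 14% or 25% of their 8-week window.** That carries the origin of the time-to-event outcome over to an item with no stated origin. The Background speaks of recurrence within 8 weeks of recovery, which points to a different reading.
- **A combined endpoint is missing.** The and/or in the hypothesis is compatible with assessing death and readmission separately, as the outcome list and the analysis section do.

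**Conclusion.** The point holds as a fault in stated definitions. Time to readmission is fixed to start before readmission is possible. It and the two time-to-death outcomes have no origin for patients who never meet two criteria. The 8-week item has no stated origin, and one-year death in Table 2 does not share the origin of the primary time-to-death outcome. Index-stay deaths are not separated from the post-discharge deaths that the set is meant to predict.

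The documents do not show that the results will be materially distorted. On the assumed rates, the effect on sensitivity and specificity for readmission is about 0 to 2 points, with observed readmission in positives about 1 to 7 points lower. The share of one-year deaths that occur in hospital, 4% to 25% on assumed mortality, is the part that could matter most. All these sizes rest on rates and lengths of stay that the article does not give. The definitions are worth correcting because they bear on the study's first objective and the correction costs very little.

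**What to change.** 1. Measure every readmission outcome (time to first readmission and readmission within 8 weeks) from live discharge from the index admission, for every patient whatever the indicator status.
2. Treat death before readmission as a competing event. Report readmission or death within 8 weeks as a sensitivity analysis.
3. Use one common origin for all death outcomes in indicator-positive and indicator-negative patients, and make the outcome list and Table 2 agree. Inclusion would serve, as would the date of the case report form, which is completed in both conditions. Discharge is not required.
4. Report index-stay deaths separately, or repeat the one-year mortality accuracy in patients discharged alive.

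Cost: changes of wording and a small amount of recoding. Dates of death and first readmission are already listed in Table 2. The discharge date is not listed there but should be in the medical files being reviewed. The one loss is that patients who die during the index stay leave the readmission analysis, where they were never at risk.

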#### Outcome measures intervention study

1. The primary outcome measure is:

a. Change in quality of life (St George Respiratory Questionnaire (SGRQ) [36]) of the patient 3 months after inclusion

2. The secondary outcome measures are:

Patient-related

a. Change in quality of life (SGRQ) of the patient 6, 9 and 12 months after inclusion

b. Change in quality of life at the end of life (McGill Quality of Life questionnaire (McGill QOL) [37]) 3, 6, 9 and 12 months after inclusion

c. Change in psychological wellbeing (Hospital Anxiety and Depression Scale (HADS) [38]) 3, 6, 9 and 12 months after inclusion

d. Change in illness understanding 3, 6, 9 and 12 months after inclusion

e. Number and length of unexpected hospital admissions

f. Number and length of unexpected ICU admissions

g. Are the choices of Advance Care Planning (ACP) documented in the medical file? (when yes/when no)

h. Place of death (ICU/hospital/hospice/nursing home/at home)

i. Is preferred place of death known? (when yes/when no)

j. Has this wish come true? (when yes/when no)

k. Length of survival of COPD patients with proactive palliative care integrated with standard care versus standard care only

Informal caregiver-related

a. Change in informal caregiver burden (Self-Perceived Pressure from Informal Care questionnaire (SPPIC) [39]) 3, 6, 9 and 12 months after inclusion

b. Change in psychological wellbeing (HADS) at 3, 6, 9 and 12 months after inclusion

c. Change in illness understanding at 3, 6, 9 and 12 months after inclusion

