#### Exclusion criteria

A patient that meets any of the following criteria will be excluded from participation:

● Not speaking the Dutch language, or

● Having severe cognitive disorders, or

● At moment of inclusion being treated by a specialized palliative care team.

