### Randomization

Randomization will not take place. Hospitals will be selected for the intervention condition based on the presence of a specialized palliative care team in the hospital. In order to be able to compare the hospitals in the control- and the intervention condition a pre-test assessment will be performed.

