### Data collection

Data collection will take place by administration of questionnaires to the participating patients and their informal caregivers and by retrospectively collecting data from the medical files of the participating patients over the assessment period. The type of questionnaires for patients and informal caregivers, the frequency of their administration and the retrospectively collected data are detailed in Table 2.

**Table 2 T2:** Overview of outcome measures per time point in the PROLONG study

**Outcome measures**	**B**	**3 m**	**6 m**	**9 m**	**12 m**	**R**

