#### Study parameter(s) intervention study

Frequencies, means and standard deviations will be used to describe the study variables. Differences between the study groups in baseline characteristics and clinical outcomes will be assessed and tested for statistical significance with the use of two-sided Fisher’s exact tests and chi-square tests for categorical variables and independent-samples t-tests for continuous variables. The primary study outcome measure of the intervention study is the change in the score on the SGRQ from baseline to 3 months: a paired *t*-test will be used to test the difference between the groups for statistical significance. Linear mixed models, with adjustment for baseline scores, will be used to study the effect of proactive palliative care on SGRQ outcomes during the follow-up period. The analysis follows the principle of intention to treat. Survival time will be calculated from the date of enrollment to the date of death with the use of the Kaplan-Meier method. A Cox proportional-hazard model will be used to assess the effect of proactive palliative care on survival, with adjustment for demographic characteristics.

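### ACP documentation is collected at baseline, but no stated analysis uses it, so a prior difference between the non-randomised hospital groups would carry into the comparison of end status

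*Protocol article*

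**What the plan says.** Under *Outcome measures intervention study*, patient-related secondary item g is "Are the choices of Advance Care Planning (ACP) documented in the medical file? (when yes/when no". It carries no time point. The same question recurs in the *Post-test assessment* list, where medical files are examined over the assessment period.

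The *Data collection* section makes Table 2 the place for detail: "the frequency of their administration and the retrospectively collected data are detailed in Table 2". Table 2 splits the question into two medical-file items:

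- "Are the choices of ACP documented in the medical file at baseline? (when yes/when no"
- "Are the choices of ACP documented in the medical file after one year or at time of death? (when yes/when no"

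Under *Study parameter(s) intervention study*, the analysis text says "Differences between the study groups in baseline characteristics and clinical outcomes will be assessed and tested for statistical significance", and the method for yes/no data is "two-sided Fisher’s exact tests and chi-square tests for categorical variables". Adjustment is named in two places only: baseline scores in the linear mixed models for the SGRQ, and demographic characteristics in the Cox model for survival.

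On allocation, *Randomization* says "Hospitals will be selected for the intervention condition based on the presence of a specialized palliative care team in the hospital". One exclusion criterion bears on prior ACP: "At moment of inclusion being treated by a specialized palliative care team".

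**The concern.** The second Table 2 item is a status. A patient whose ACP choices were on file before the admission and are still there a year later is a yes on it, and so is a patient whose choices were first recorded during follow-up. Only the second patient tells us anything about the intervention. The baseline item can separate the two, but the article gives it no role in the comparison.

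This would matter less in a randomised trial. Here the feature that defines the intervention hospitals, an existing palliative care team, is a plausible cause of different ACP practice before the study began. The one-year *Pre-test assessment*, meant to let the hospitals be compared, covers admissions, patients, days and deaths, with no ACP item. Baseline ACP is also absent from the confounders listed under *Other study parameters* and *Post-test assessment*.

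The Background names ACP as a core part of good proactive palliative care, so this outcome is close to a direct measure of what the intervention delivers. A prior difference in practice could be read as an effect. If the control hospitals started higher, it could hide one.

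**Working it through.** **1. Where the baseline item could enter the analysis.**

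| Place in the article | Use of baseline ACP status |
|---|---|
| Outcome list, item g | none; no time point |
| *Post-test assessment* list | none; files examined over the assessment period |
| Table 2 | collected as its own item |
| *Other study parameters* and post-test confounders | not listed |
| *Pre-test assessment* (hospital level) | no ACP data |
| Fisher / chi-square sentence | unadjusted; ACP not named |
| SGRQ mixed models | adjust for baseline scores; another outcome |
| Cox model | adjusts for demographics; another outcome |

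The item is collected, but no stated between-group comparison conditions on it.

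**2. Size of the carry-over.** The documents give no ACP rate, so there is no planned figure to reproduce. Every rate below is an assumption. Only the 86 per arm comes from *Sample size calculation*.

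Let *b* be the proportion documented at baseline and *q* the proportion of undocumented patients who become documented. Assume documentation is not lost once made. Then

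end status = *b* + (1 − *b*)*q*.

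With the same *q* in both arms (no effect), the difference in end status is

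(1 − *q*)(*b*_intervention − *b*_control).

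With *q* = 0.20, four fifths of any baseline gap passes into the end-status difference:

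- 10% vs 5%: 0.10 + 0.90 × 0.20 = 0.28; 0.05 + 0.95 × 0.20 = 0.24; spurious difference 4 points.
- 20% vs 10%: 0.20 + 0.80 × 0.20 = 0.36; 0.10 + 0.90 × 0.20 = 0.28; spurious difference 8 points.
- Equal baselines: difference 0.

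**3. Rejection rate.** Exact calculation: two independent binomials of 86, two-sided Fisher's test at 0.05, clustering by hospital ignored.

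| Assumed baseline | End status | Spurious difference | Rejection |
|---|---|---|---|
| 10% vs 5% | 28% vs 24% | 4 points | about 6.5% |
| 15% vs 10% | 32% vs 28% | 4 points | about 6.5% |
| 20% vs 10% | 36% vs 28% | 8 points | about 16% |
| 10% vs 10% | 28% vs 28% | 0 | about 3% |

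Fisher's test is conservative here, so about 3% is the right comparator, not 5%.

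**4. The same data restricted to patients undocumented at baseline.** Both arms then have expected proportion *q*, so the difference is 0 whatever the baseline gap. With 20% vs 10% documented at baseline, the expected numbers left are 86 × 0.80 ≈ 69 and 86 × 0.90 ≈ 77, and Fisher's test rejects in about 4%.

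**The case against.** The strongest objection is that the article never says how the ACP outcome is tested. The Fisher and chi-square sentence is generic and does not name ACP. It could apply to end status, or equally to new documentation among patients undocumented at baseline. Collecting a separate baseline item suggests that someone meant to use it, and the post-test wording about the assessment period could be read as counting only new entries. How a baseline item enters one secondary outcome is often left to an analysis plan.

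Much of this stands. A reader might infer that patients documented before the study are scored as intervention successes. No section says so; that follows only if the generic test is applied to end status. A reader might also infer large error inflation. Baselines of 40% vs 20% would give 16 points and about 52% rejection, and 50% vs 20% would give 24 points and about 87%. The documents give no basis for gaps of 20 to 30 points. The Background says ACP discussions are unlikely to occur, the Discussion says COPD patients hardly receive palliative care, and patients already under a specialised palliative care team are excluded. That exclusion narrows the route to imbalance without closing it, because lung specialists and others can also record ACP choices.

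The point about the method remains. Where the article wants adjustment it says so, for the SGRQ and for survival. For categorical outcomes it states an unadjusted test. Collecting a variable does not adjust for it, and comparing baseline ACP between arms would show an imbalance but not correct it.

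**Conclusion.** The concern holds in a limited form. For ACP documentation, the stated method is an unadjusted between-group test, and the baseline item in Table 2 enters no stated comparison. Because allocation follows the presence of a palliative care team, a baseline difference is plausible, and it would pass into the end-status comparison.

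The size is unknown. It depends on an assumed baseline gap, an assumed 20% new-documentation rate equal in both arms, 86 patients per arm, and no allowance for clustering. Gaps of 5 to 10 points give spurious differences of 4 to 8 points and rejection of about 6.5% to 16%. With equal baselines there is no bias.

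The documents do not support the stronger claim that the plan counts prior documentation as success. The primary outcome, the sample size and the survival analysis are untouched. This is a cheap improvement to one secondary outcome.

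**What to change.** Choose one of two changes:

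- In *Study parameter(s) intervention study*, state that ACP status at one year or death is compared with a model that adjusts for baseline ACP status.
- Or, in item g of the outcome list and in the *Post-test assessment* list, define the outcome as ACP choices newly documented between baseline and one year or death, among patients with none documented at baseline.

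In either case, report crude end status by arm descriptively, next to the baseline proportions.

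The cost is a sentence or two of wording; both items are already abstracted from the medical files. The new-documentation version uses fewer patients, for example about 69 and 77 instead of 86 and 86 at assumed baselines of 20% and 10%. Neither version removes other differences between non-randomised hospitals; each deals only with documentation that existed before the study.
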